### **11.1 Monitoring of adverse events**

All events, whether reported by subjects or investigators, or detected by physical examination or laboratory results, will be managed and collected in compliance with all applicable regulations and will be included in the final Clinical Study Report (CSR).

### **11.2 Definitions of adverse events**

#### **11.2.1 Adverse event (AE)**

Adverse Events, regardless of their relationship to Investigational Product, as long as they occur from the first visit planned in the Clinical Trial Protocol/signature of the informed consent (i.e., occurring during the washout period) to the last visit planned in the protocol, are adverse medical events or deterioration of qualifying event. AEs include symptoms (ie, nausea, chest pain), signs (ie, tachycardia, liver enlargement) and abnormal laboratory results (ie, laboratory or ECG abnormalities). AEs can be classified as serious AEs and non-serious AEs.

#### **11.2.2 Serious adverse event (SAE)**

A Serious adverse event is refers to any untoward medical occurrence that at any

dose:

- Results in death, or
- Is life-threatening, or

**Note: The term “life-threatening” in the definition of “serious” refers to an event in which the patient is at risk of death at the time of the event; it does not refer to an event which hypothetically might have caused death if it was more severe.**

- Requires inpatient hospitalization or prolongation of existing hospitalization, or
- Results in persistent or significant disability/incapacity, or
- Is a congenital anomaly/birth defect, or
- Is a medically important event

### 11.3 Recording of adverse events

Only some of the non-serious AEs (ie, bleeding events, dyspnea, asthma, renal impairment/increased blood creatinine, bradycardia, increased liver function test indicators, gout/increased uric acid, pneumonia, gynecomastia, abnormal uterine bleeding, malignant tumors) and discontinuations of the study medication due to adverse events (DAEs) will be collected from time of randomization throughout the treatment/follow-up periods to the Study Closure Visit. Other non-serious AEs are up to the investigator to decide whether to collect.

SAE: All SAEs will be collected and recorded.

### 11.4 Causal relationship between adverse events and study drugs:

Attribution of : ①Definite; ②Probably; ③Possibly; ④Unlikely; ⑤Not related;

⑥Not accessible. Definitions are as follows:

① **Definite:** Causal relationship is certain (i.e., the temporal relationship between treatment exposure and the adverse event onset/course/resolution is clinically

reasonable; other causes have been eliminated; and the event must be definitive pharmacologically or phenomenologically). The adverse reaction is alleviated or disappeared after the reduction of drug dose or discontinuation of the drug. The reaction reappears when the drug is re-initiated.

② **Probably:** High degree of certainty for causal relationship (i.e., the temporal relationship between treatment exposure and the adverse event onset/course/resolution is clinically reasonable and other causes have been eliminated or are unlikely). The adverse reaction is alleviated or disappeared after the reduction of drug dose or discontinuation of the drug. The subject's clinical status or other reasons could cause this reaction.

③ **Possibly:** Causal relationship is uncertain (i.e., the temporal relationship between treatment exposure and the adverse event onset/course/resolution is clinically reasonable or unknown; and while other potential causes may or may not exist, a causal relationship to the study treatment does not appear probable). The adverse reaction is alleviated or disappeared after the reduction of drug dose or discontinuation of the drug. The subject's clinical status or other reasons could possibly cause this reaction.

④ **Unlikely:** Not reasonably related, although a causal relationship cannot be ruled out (i.e., while the temporal relationship between treatment exposure and the adverse event onset/course does not preclude causality, there is a clear alternate cause that is more likely to have caused the adverse event than the study treatment). The subject's clinical status or other reasons could possibly cause this reaction.

⑤ **Not related:** No possible relationship (i.e., the temporal relationship between treatment exposure and the adverse event onset/course is unreasonable or

incompatible; or a causal relationship to study treatment is implausible). The subject's clinical status or other reasons could possibly cause this reaction. After clinical symptoms or other causes resolved, the reaction is alleviated or disappeared.

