### **7.6 Temporary/permanent discontinuation of the study drug(s) or loss of follow-up**

The study drug(s) should be continued whenever possible. If the study drug(s) are stopped, it should be determined whether they can be stopped temporarily; permanent study drug(s) discontinuation should be a last resort. Any study drug discontinuation should be fully documented in the CRF. Discontinuation of study medication does not mean discontinuation of follow-up or termination of study participation. In any case, the patient should stay in the study as long as possible.

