### **7.6.1 Temporary treatment discontinuation of the study drug(s)**

If the study drugs must be temporarily discontinued, they should be re-started as soon as possible:

Including the following conditions:

- 1) Severe thrombocytopenia (platelet count <50,000/uL). Patients may restart study

medication once the severe thrombocytopenia resolves;

- 2) Severe bleeding (GUSTO definition);
- 3) Need of treatment with prohibited concomitant medications, see Section 7.5;
- 4) Surgery or procedures associated with major haemorrhage, see Section 7.5.3;

For other surgery or other invasive procedures, study medication may be continued or interrupted temporarily at the discretion of the investigator.

Once the Investigator has considered that the role of the Investigational Product(s) in the occurrence of the event concerned is unlikely and there are no other contraindications to prevent its(their) continued use in the study. Treatment with the Product can be re-initiated under close and appropriate clinical/and or laboratory monitoring.

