**⑥ Not accessible**

Total rate of AE will be calculated by summarizing the incidence of adverse drug events in each case report form ①+②+③.

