### **3. Safety analysis**

All patients who receive at least 1 time study drugs and safety assessment will be included in the safety analysis set. The safety evaluation data include adverse events observed during the trial and changes in laboratory data before and after treatment. Adverse events will be summarized using descriptive statistics. And the differences in the primary safety endpoints, secondary safety endpoints and the incidence of various adverse reactions will be compared between the two treatment arms. In addition to comparing the mean of laboratory indicators before and after treatment, we will also list the specific conditions of ~~those been~~ normal before treatment but ~~became~~ abnormal after treatment.

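### Protocol 11.4 makes improvement off drug a condition of every drug-related grade, so fatal, irreversible and treated-through reactions drop out of the drug-related rate

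*Supplement*

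**What the plan says.** Section 11.4 of protocol v1.4 presents its six categories as definitions.

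- **Definite, Probably and Possibly** each contain, word for word, "The adverse reaction is alleviated or disappeared after the reduction of drug dose or discontinuation of the drug". There is no exception for events in which this cannot be observed.
- **Definite** adds "The reaction reappears when the drug is re-initiated".
- **Possibly** is looser on timing, "the temporal relationship between treatment exposure and the adverse event onset/course/resolution is clinically reasonable or unknown", but the improvement sentence still follows.
- **Unlikely** needs an alternative explanation: "there is a clear alternate cause that is more likely to have caused the adverse event than the study treatment".
- **Not related** needs incompatible timing or an implausible link.
- **"Not accessible"** is listed without a definition.

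The section ends by forming the total adverse event rate from the first three categories only.

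Three other parts of the protocol bear on this. Section 7.6 says "The study drug(s) should be continued whenever possible". Section 7.6.1 ties restarting to a judgement on causality: "Once the Investigator has considered that the role of the Investigational Product(s) in the occurrence of the event concerned is unlikely". Section 13.3.2, item 3, says "the incidence of various adverse reactions will be compared between the two treatment arms".

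**The concern.** Improvement after withdrawal is useful evidence of causality when it can be observed. It cannot be observed when the patient dies, when the damage is permanent, or when drug was never stopped. Written as a condition of every counted grade, it makes relatedness depend on the outcome of the event and on what was done with the drug.

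Such events are foreseen. Section XI lists hemorrhagic stroke among the side effects of ticagrelor. Section 11.2.2 names death and lasting disability as criteria of seriousness. Section 7.6 encourages continued treatment.

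At stake is a drug-related rate that omits the gravest reactions and depends partly on who stops drug. The rate is also labelled as the total rate of adverse events although it covers only those judged drug-related, so a reader could take it for complete.

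**Working it through.** There is no figure to reproduce, because the question is one of wording. The check takes three kinds of event through the six definitions. In each case the timing is plausible and there is no clear alternative cause.

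| Event | Definite, Probably, Possibly | Unlikely | Not related | What is left |
|---|---|---|---|---|
| Fatal haemorrhage | Fails: no improvement can follow | Fails: no clear alternative cause | Fails: timing compatible, link plausible | Not accessible |
| Disabling hemorrhagic stroke with no improvement after stopping | Fails: the condition persists | Fails, same reason | Fails, same reason | Not accessible |
| Bleed or dyspnea that settles with drug continued | Fails: no reduction or stop preceded recovery | Fails, same reason | Fails, same reason | Not accessible |

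**Count.** The rule at the end of 11.4 is rate = (category 1) + (category 2) + (category 3). All three rows end in category 6, so each contributes 0.

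**Can Definite be reached?** It needs recurrence on restarting. The general rule in 7.6.1 allows restarting once the drug's role is thought unlikely, which pulls against a Definite grade. There are other routes, though. Item 1 of 7.6.1 lets a patient with severe thrombocytopenia restart after it resolves and attaches no causality judgement to that item. Sections 7.5.1 (after thrombolysis) and 7.5.3 (after surgery) have restart conditions of their own. Definite is therefore hard to reach but not impossible.

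**How common is the third row?** Section 7.6 favours continuing drug. Section 11.5.3 says medication is interrupted or withdrawn when an adverse event occurs. The two conflict, and the frequency of treated-through events depends on which one sites follow. The first two rows do not depend on this.

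**Does another section repair it?** Section 11.5.1 asks the investigator for an opinion on whether the product may have caused the event, with no improvement condition. It is not linked to the six categories or to the rate. SAP v1.3 gives no other definition of relatedness.

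**The case against.** The strongest objection is that little of the safety analysis rests on causality. Section 13.3 leaves the planned analyses to the SAP. Section 13 of SAP v1.3 contains no causality-based table or test:

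- adverse events are compared by system organ class and preferred term;
- bleeding is compared by GUSTO grade;
- deaths are compared by Fisher's exact test;
- all deaths and serious events receive narratives.

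This stands, and it sets the limit of the point. A reader might infer that fatal or disabling haemorrhages vanish from the safety results. They do not. Severe or moderate bleeding is the primary safety endpoint, mortality and serious events are secondary safety endpoints, and hemorrhagic stroke is also part of the primary efficacy endpoint.

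The adverse-reaction comparison in 13.3.2 does not cite the 11.4 categories, so its dependence on them is possible rather than stated.

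The improvement sentence could also be read as descriptive, since Possibly tolerates unknown timing. But nothing marks it as optional. If some sites treat it as a condition and others do not, grading will differ between sites.

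A reader might further infer that only reactions leading to early stopping can be counted, so that the related share is capped by the stopping rate and the arms are distorted by a calculable factor. The documents do not support this. They give no stopping rate. Every patient ends study drug at about day 90, while adverse events are collected to 12 months, so a reaction still present at the end of treatment can meet the condition later.

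Nor is Probably self-contradictory: a cause judged unlikely is still one that could have acted.

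**Conclusion.** The point holds as a defect in the definitions. On the text of 11.4, reactions that are fatal, that do not improve, or that settle on continued drug cannot be graded as related. Without a clear alternative cause they end in an undefined category outside the count. For fatal and non-improving reactions this follows from the wording alone. For treated-through reactions the logic is the same, but their number depends on the unresolved conflict between 7.6 and 11.5.3.

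The effect is confined to the drug-related rate in 11.4 and to any comparison under 13.3.2 that uses it. No magnitude, and no direction of bias between the arms, can be derived from the documents. The conclusion assumes that the improvement sentence is applied as the condition it appears to be. The correction is worth making because the rate is wrong as specified and costs almost nothing to mend.

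**What to change.** In section 11.4 of the protocol and the matching CRF guidance:

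1. Apply the improvement and recurrence criteria only where they can be assessed, and state that they do not apply when the event was fatal or irreversible or when drug was continued.
2. Grade those events on timing, pharmacological plausibility and alternative causes.
3. Define the sixth category and say how its events enter the drug-related count.
4. Relabel the sum of categories 1 to 3 as the rate of drug-related adverse events.
5. In 13.3.2, item 3, say whether the adverse-reaction comparison uses these grades.

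Separately, reconcile 7.6 with 11.5.3 on what happens to study drug when an adverse event occurs. This review takes no position on which should prevail.

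The cost is wording only. Section 11.5.1 already has sites record onset, outcome, action taken with the product and an opinion on causation, so no new data are needed.

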**⑥ Not accessible**

Total rate of AE will be calculated by summarizing the incidence of adverse drug events in each case report form ①+②+③.

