## **2) Secondary safety endpoints**

- Incidence of severe bleedings or moderate bleedings (GUSTO definition) at 1 year;
- Bleeding events (severe or moderate bleedings or intracranial hemorrhage) at 3 months and 1 year;
- Mortality at 3 months and 1 year;
- AEs/SAEs reported by the investigators at 3 months and 1 year.

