## **13.3 Statistical considerations**

This section is an overview of the statistical considerations. It provides the general specifications for the analysis of the data to be collected and presented in the Clinical Study Report. A final SAP will be issued prior to database lockdown and before code breaking. The SAP will define all “pre-specified, planned analyses.”

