### **Adverse Events**

Adverse events (AEs) will be coded using the MedDRA coding dictionary (Version 6.0 or a later release) and grouped by system organ class (as detailed in the study protocol).

Separate data display listings and summaries will be presented for adverse events that start prior to first dose of study medication (pre-treatment), whilst on study medication (during treatment) and after the last dose of study medication (post-treatment).

Within each treatment group, the number and percentage of subjects experiencing an AE will be summarized by system organ class and preferred term and Fisher's Exact test will be used to compare the number of each grouped AE event between treatment groups. In addition, a separate summary will be provided for AEs experienced by more than 5% of subjects in either of the treatment groups.

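### Protocol section 11.4 calls a drug-related rate the total adverse event rate, contradicting the protocol's own AE definition and the causality-free AE endpoint

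*Supplement*

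**What the plan says.** Protocol v1.4, section 11.4, sets out an attribution scale: "①Definite; ②Probably; ③Possibly; ④Unlikely; ⑤Not related", then a sixth level, not accessible, which has no definition. The section closes with the rule "Total rate of AE will be calculated by summarizing the incidence of adverse drug events in each case report form ①+②+③".

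Other places in the current documents describe AEs without a causality condition:

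- Protocol 11.2.1 defines them as "Adverse Events, regardless of their relationship to Investigational Product", subject only to a time window.
- Protocol 4.3 lists as a secondary safety endpoint "AEs/SAEs reported by the investigators at 3 months and 1 year". SAP v1.3, section 3, repeats it.
- SAP v1.3, section 13, Adverse Events, says that "the number and percentage of subjects experiencing an AE will be summarized by system organ class and preferred term". Arms are compared by Fisher's exact test, and a further summary covers AEs seen in more than 5% of either arm. Attribution is not mentioned.

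Two further places bear on how the rule fits in. The safety analysis in protocol 13.3.2 says that "secondary safety endpoints and the incidence of various adverse reactions will be compared between the two treatment arms", so endpoints and reactions are named as two items. Protocol 13.3 leaves the detail to the analysis plan: "A final SAP will be issued prior to database lockdown and before code breaking".

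**The concern.** A rate called total should cover every event that the protocol counts as an AE. This one covers three of six attribution levels. The omitted levels are not all clear negatives. The protocol's description of unlikely concedes that a causal link cannot be excluded, and not accessible presumably means that no judgement could be made.

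The counting unit is also open. The rule could mean adding three category incidences, or counting each patient's case report form once if it holds any event in the three categories. Only under the first would a patient with both a possible and a probable event count twice.

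At stake is the headline AE figure in the study report. Someone asked for the total AE rate would find one formula, and it does not match the endpoint in 4.3. Readers could take a rate filtered by investigators' opinions for the overall AE burden of two antiplatelet regimens.

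**Working it through.** **Step 1. Passages side by side.**

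| Place | Quantity | Causality filter | Counting unit |
|---|---|---|---|
| Protocol 11.2.1 | definition of an AE | none | event |
| Protocol 4.3, SAP section 3 | AEs/SAEs as secondary safety endpoint | none | not stated |
| Protocol 11.4 | total AE rate | definite, probably, possibly only | not stated |
| SAP section 13 | AEs by class and term | none | subject |

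The 11.4 rate differs from every other row in scope. SAP section 13 neither repeats nor withdraws the rule, and it specifies no overall row for subjects with any AE. Section 11.4 therefore holds the only explicit total.

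**Step 2. Size.** The documents state no AE rate and no split by attribution, so there is no figure to reproduce. What follows is an illustration on assumed incidences, with categories treated as independent.

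Let p1, p2, p3 be the shares of patients with a definite, probable and possible event, and q the share with an event in the three omitted categories.

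- Simple sum: s = p1 + p2 + p3
- Patients with at least one related event: r = 1 − (1 − p1)(1 − p2)(1 − p3)
- Patients with any AE: a = 1 − (1 − r)(1 − q)
- Shortfall of a patient-level 11.4 rate: a − r = q(1 − r)

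Worked case, p = 1%, 2%, 7% and q = 10%:

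- s = 10.0%
- r = 1 − 0.99 × 0.98 × 0.93 = 9.77%
- a = 1 − 0.9023 × 0.90 = 18.79%
- a − r = 9.02 points; s − r = 0.23 points

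| p1 / p2 / p3 | s | r | s − r (points) | a − r, q = 2% | a − r, q = 10% | a − r, q = 20% |
|---|---|---|---|---|---|---|
| 0.5 / 1 / 3% | 4.5% | 4.45% | 0.05 | 1.91 | 9.55 | 19.11 |
| 1 / 2 / 7% | 10.0% | 9.77% | 0.23 | 1.80 | 9.02 | 18.05 |
| 2 / 5 / 15% | 22.0% | 20.87% | 1.13 | 1.58 | 7.91 | 15.83 |

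**Step 3. Reading the table.** The omission is close to q itself. The possible double counting adds 0.05 to 1.13 points and works in the opposite direction. It comes near to cancelling the omission only where related events are common and omitted ones rare: in the last row with q = 2%, s = 22.0% against a = 22.45%. Elsewhere the omission dominates.

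**Step 4. What does not use the rule.** SAP section 13 compares subjects with AEs by class and term whatever the attribution. It tabulates SAEs and gives a narrative for every death and SAE. Moderate or severe GUSTO bleeding and intracranial haemorrhage are endpoints irrespective of attribution.

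**The case against.** The strongest reply is that the sentence is a stray descriptive line at the end of the causality section. It is not tied to the endpoint in 4.3. Protocol 13.3.2 names endpoints and adverse reactions separately, and the three-category figure fits the second. Protocol 13.3 hands the planned analyses to the SAP, whose AE analysis counts subjects without a filter. Protocol 11.1 puts all events in the study report, and 11.5.1 has the investigator's causality opinion recorded, so no data are lost.

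Most of this stands, and it rules out three stronger inferences that a reader might draw:

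- That the AE endpoint itself leaves out unlikely, unrelated and unassessed events, so that the comparison between arms becomes one of causality opinions. No passage makes the 11.4 rate the analysis of that endpoint, and the SAP's comparison has no such filter.
- That an SAE rated unlikely, or a serious bleed rated not accessible, disappears. It is absent only from the 11.4 figure; the SAE tables and bleeding endpoints still capture it.
- That patients are certainly counted twice. The reference to each case report form can equally mean one count per patient.

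The reply does not rescue the rule. SAP section 1 tells its users to consult the protocol alongside it, and nothing there overrides 11.4. The split in 13.3.2 shows that the protocol recognises two quantities, and 11.4 gives the name of the first to the second.

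**Conclusion.** The rule is wrong as labelled. Protocol 11.4 calls a drug-related rate the total AE rate, omits three of six attribution levels, leaves the counting unit open, and conflicts with 11.2.1, with 4.3 and with the unfiltered subject-level analysis in SAP section 13.

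The damage is confined to the overall AE rate reported under 11.4. The primary efficacy endpoint, the primary safety endpoint (moderate or severe GUSTO bleeding), mortality, the SAE tables and the SAP's comparison by class are unaffected.

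The size cannot be known from the documents. Under the assumptions above, the shortfall is about 1.6 to 1.9, 7.9 to 9.6 and 15.8 to 19.1 percentage points when 2%, 10% and 20% of patients have an event in the omitted categories. These figures follow from the assumed incidences and from independence between categories. They show scale and do not predict the trial's result.

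**What to change.** - In protocol 11.4, define the total AE rate as the number of patients in the safety set with at least one collected AE of any causality, divided by the number in the safety set, by arm. This agrees with the subject-level count in SAP section 13. The word collected matters because protocol 11.3 requires only certain non-serious AEs to be captured.
- Add that overall row to SAP section 13, which at present goes straight to class and term.
- Rename the three-category figure the drug-related AE rate, and count each patient once.
- Show not-accessible events on a separate line.

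The cost is a sentence or two in the protocol and one table row in the SAP. No new data are needed, since attribution is already recorded. The reported total will normally be higher than under the present rule.
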